**Fig. 1 Fig1:**
[figure not shown]
The flowchart of experimental vs. control situations in the study design

## Recruitment and sampling

The recruitment of schools was based on three aspects. First, voluntariness, i.e., their (headmasters and teachers’) self-defined need for intervention, knowledge, and training on psychosocial skills while teaching refugee and immigrant adolescent students. For that purpose, the first recruitment was through advertisement in the national teachers’ magazine (Opettaja) and email lists to school administration in every municipality in Finland. Second, the recruited and voluntary schools should have a considerable share of refugee and immigrant background pupils in secondary school classes estimated as 30–50% in each class. Third, the schools accepted the possibility of serving as a waiting list school until the next school year when they would be provided the INSETT intervention in electronic form. The first wave of recruitment was complemented with about 100 phone calls to headmasters of schools residing in the metropolitan or otherwise immigrant-dense areas of larger cities in Finland. In the second wave of recruitment, phone calls and e-mail communications were established to invite schools close to asylum centers in numerous towns and municipalities in Finland. However, most extra work to reach schools near asylum centers and the metropolitan area was not successful as schools informed that they already had several general interventions (such as anti-bullying whole-school programs) or trauma and refugee-focused programs (such as cultural coaching programs). As a result of the two waves of recruitment, 16 schools agreed to participate in the Refugees Well School study.

Table 1 presents the study period for implementing interventions, collecting data (T1, T2, T3), and specific measures for adolescents, teachers, and parents. Baseline data was collected before the interventions, INSETT+TRT and PIER interventions were implemented between September 2019 and January 2020, post-intervention data collection took place around February 2020, and the follow-up data will be collected in August 2020. INSETT will be provided to waiting list control schools in October 2020.

## Eligibility criteria

The unit of recruitment was schools. As both the INSETT+TRT and PIER interventions aim at enhancing school belonging, high peer quality, interethnic friendships, and understanding and protecting cultural diversity, we included both native-Finnish and refugee-immigrant adolescents in the interventions and effectiveness study. The only exclusion criterion for schools was not to have other similar psychosocial interventions running at the same time. For students, there were no exclusion criteria, and all who signed the informed consent could participate. The 16 schools were located across the country of Finland and represented mainly refugee and immigrant-dense urban areas. One school is in the south, (the metropolitan area), two in the east, three in the middle, two in the west, and three in northern Finland. If a participant should not want to continue participating in the study, she/he may resign simply by informing the researchers, and the given participant data would be deleted from the system. If intervention participation would cause harm to a participant, she/he would be advised to appropriate services. The participation was not expected to cause harm to the participating individuals, since the interventions had been shown to increase well-being and decrease mental health symptoms in the previous studies [45]. In the baseline data collection phase, the researchers stayed at the study site and were ready to discuss with the students if they felt distressed after filling the survey. Reported experiences of caused harm will be stored anonymously and described in the results.

## The interventions

In-service Teacher Training (INSETT) is developed by [name] and it is designed for lower and upper secondary school teachers and counselors in introductory-, preparatory-, and ordinary classes [46]. The INSETT aims at enhancing teachers’ cultural competence concerning refugee experience and self-efficacy via teachers’ education, cultural awareness, and peer support practices. After INSETT, we expect teachers’ improved skills to induce positive changes in three key areas: [1] promoting and supporting mental health and well-being among trauma-affected students with refugee and migration backgrounds, [2] encouraging students in positive interethnic relationships in linguistically and culturally diverse school settings, and [3] fostering relationships between teachers and parents/caregivers to promote co-operation and involvement with schoolwork. The teachers’ training and awareness building is expected to benefit the well-being and sense of belonging of refugee and immigrant students directly and their caregivers indirectly.

The intervention involves a combination of two seminar days with lectures, discussions, exercises, and exchange of ideas and experiences between participating teachers, and an online training course to be completed by teachers individually. The INSETT intervention provides seminar topics, materials, and literature to prepare thematic sessions, and slides [46], and the online training course *Providing support to refugee minors* by the Augeo Foundation in the Netherlands [47] and extensive local-language material to schools in Finland, Norway, and Sweden.

*Peer Integration and Enhancement Resource (PIER)* is delivered by lower and upper secondary school teachers, counselors, and special teachers in school classes including both native and refugee and immigrant students. The PIER aims at supporting safe and positive peer interactions and social relationships in multi-ethnic schools. This is expected to happen through group exercises that focus on strengthening the sense of belonging, empathy, and role-taking; learning from each other; and getting and giving more social support. The manualized intervention consists of eight sessions ranging between 45 and 90 min. Sessions include structured welcoming and ending rituals and multi-modal group activities such as cartoon drawing, role-play, movies, and drama. Sessions also include practices of reflecting various identities, migration, and racism.

The school staff delivering the PIER participated in a 2-day training. The first day included practicing each intervention session and going through the resource material. The second day included sharing experiences and valuable ideas to improve the intervention.

*Teaching Recovery Techniques (TRT)* is a TF-CBT-based, manualized group treatment developed by the Children and War Foundation [48]. The core aim of this intervention is to create a sense of safety and increase feelings of competence and shared hope. In more detail, the aims are to reduce PTSD symptoms of intrusion, avoidance, and hypervigilance; increase resilience; stabilize trauma reactions; and provide practical techniques and strategies to deal with traumatic memories, physical and behavioral arousal, and withdrawal. Treatment elements include psychoeducation (in playful and multi-modal ways), normalizing reactions to trauma, working with nightmares, mastering intrusive memories and trauma reminders with framing techniques, and dealing with avoidance and arousal with scaling techniques. Homework such as sleep hygiene or reflective observation of trauma reminders is an essential part of the TRT.

The TRT consists of five sessions of 90 to 120 min including skills training, rehearsal, and homework, and the handbook provides each session with several tools, techniques, and procedures. The two sessions for parents or caregivers include information about various responses to traumatic events and effective coping strategies. School personnel delivering the TRT participate in 2-day intensive training provided by a licensed trainer either from the Children and War Foundation or from Finland. Qualified trauma psychologists offer work counseling to TRT group leaders during the intervention.

## Data collection and management

Survey data is collected online from students, teachers, and parents, and informed consent is collected both on paper and online at the beginning of the survey. Foreign-speaking parents receive both online and paper surveys, and the informed consent form is both on paper and online. The online survey is managed using a secure online survey tool [49], and all identifiable information will be stored separately from the research data. The researcher team will collect informed consent first in schools and later via mail. To avoid attrition, participants will receive a personal invitation via e-mail and two reminders to answer the post-intervention (T2) and follow-up (T3) surveys. The RWS consortium will manage and store the research data and will have a common data management plan available online.

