## Trial design

The study is a three-arm clustered parallel assignment, quasi-randomized, controlled trial (RCT) comparing INSETT+TRT and PIER to the wait list control group. The cluster is designed by the school. The schools were allocated into intervention groups or a control group using quasi-randomized design: The voluntary schools were first grouped based on whether they offered an introductory class or not. The TRT is targeted at recently arrived youth with a refugee background, and the PIER is targeted at mixed classes. The schools in the two groups were then randomly allocated to either intervention or control conditions using a random number generator [44]. The allocation aimed at equal numbers of schools in each condition. Due to the low participation rate, recruitment of schools was continued, which resulted in three additional schools all with introductory classes. The three additional schools were thus randomized either into the INSETT+TRT or control group. Blinding of participants, intervention providers, outcome assessors, or data analysts was not possible due to the explicit nature of interventions and a low number of project members. The decisions of data collection, recruitment, and training are discussed with other partners in the RefugeesWellSchool consortium but allowing each country to adopt the processes in the national framework. The control schools will receive the INSETT intervention toolkit after the research part of the project has ended. The trial aims to follow SPIRIT guidelines in reporting. Table 1 presents the SPIRIT figure, and the checklist can be found as an attachment.

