## Study setting and participants

Power calculations were conducted before the data collection started. With alpha set at 0.05, power at 0.80, and rho = 0.05 (the intra-cluster correlation), a sample size of at least 40 clusters (i.e., schools) with 25 youths each was identified as necessary. Therefore, 500 youths per study arm (i.e., intervention or wait list control) were needed, resulting in 1500 total participants. To account for an expected drop-out rate of 20%, 1800 youths would have been recruited in total. To facilitate the recruitment of so many participants, recruitment was split between the Finnish study team and our team partners in Sweden.

The interventions were implemented in lower secondary schools with grades 7–9 and/or introduction classes for newcomer youth. We focused on immigrant youth who have resided in Finland for less than 6 years. Figure 1 presents the flowchart of the recruitment. Seventeen schools expressed their interest in participating in the study, but after allocation, one school dropped out. According to the randomization, eight schools were allocated into the INSETT+TRT intervention, three schools were allocated into PIER, and five schools served as waiting list controls. Also, Fig. 1 reports the numbers of students, teachers, and parents who answered the survey in the first round of data collection.

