In the core model (Fig. 2), there are two latent state variables, measuring true scores of PRE- and POST-intervention levels of the outcomes. The PRE-intervention state is indicated by the measured T1 variable without time-related measurement error because there is only one measurement point. In the case of POST-intervention state, there are two indicators, enabling the modeling of measurement error. The loadings of the indicators in the measurement part of the model are fixed to 1’s, meaning that the trajectory from T1 to T3 has the same shape for every individual. Only the level of PRE-intervention state and the difference between PRE- and POST-intervention states are random so that the means and variances of these variables within and between the clusters can be estimated. As predictors of the POST-intervention state, our model specifies the PRE-intervention state (path coefficient *a*, which is anticipated to be negative due to floor and ceiling effects), a dummy for intervention/control group membership (direct effect *c*), and potential mediating variables (path coefficient *e*, implying indirect effect *d*e* for intervention-control-group difference). The covariance between the PRE-intervention state and the dummy for intervention/control group membership (parameter *b*) is supposed to be 0, indicating that the randomization was successful. Moderation mechanisms are investigated by estimating the model simultaneously in groups created according to categorized moderator variables (multi-group SEM). Finally, the simple estimates of total intervention effects are calculated from a model without mediators and moderators (parameter *c* divided by the variance of POST-intervention latent variable, giving an equivalent to Cohen’s *d*).

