## Trial status

This is the first version of the study protocol (dated 1 July 2020). Recruitment began in January 2019 and was completed in August 2019. The data collection ended in September 2020, and the protocol was submitted before that.

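### A zero covariance between baseline level and arm does not show that randomisation succeeded, and the total-effect model adjusts only for the same outcome's baseline

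*Protocol article*

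**What the plan says.** All of these places are in the Protocol article.

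- **Allocation (Trial design).** Schools are the unit. They were first grouped by whether they had an introductory class: "The schools in the two groups were then randomly allocated to either intervention or control conditions using a random number generator". Recruitment then continued and brought in three more schools, all with introductory classes: "The three additional schools were thus randomized either into the INSETT+TRT or control group". The same section says that blinding of participants and staff was not possible.
- **Schools (Study setting and participants).** "Seventeen schools expressed their interest in participating in the study, but after allocation, one school dropped out". The final split is 8 schools to INSETT+TRT, 3 to PIER and 5 to the waiting list.
- **Who is in the pupil sample (Eligibility criteria).** "For students, there were no exclusion criteria, and all who signed the informed consent could participate".
- **Consent (Data collection and management).** For students, teachers and parents, "informed consent is collected both on paper and online at the beginning of the survey". The section adds: "The researcher team will collect informed consent first in schools and later via mail".
- **Dates.** Trial status: "Recruitment began in January 2019 and was completed in August 2019". The Discussion puts the baseline survey in August to September 2019. Recruitment and sampling puts delivery between September 2019 and January 2020.
- **Analysis (Analytic strategy, text after Fig. 2).** The covariance b between the PRE state and the arm dummy "is supposed to be 0, indicating that the randomization was successful". The POST state is predicted by the PRE state, arm and, where used, mediators. Total effects come from the model without mediators and moderators. The Fig. 2 legend lists sociodemographics as moderators and CRIES-8 as a mediator.

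**The concern.** The plan uses baseline equality as evidence about the randomisation. In a cluster trial where pupils enter by consenting, equality among consenters reflects at least three things: how schools were allocated, how they were grouped before allocation, and who agreed to take part in each arm. A value of b near zero does not vouch for any one of them, and a value away from zero does not show that randomisation failed.

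This affects what can be concluded. A reader told that b is close to zero would take the arms as comparable on everything, when only the outcome's own baseline has been compared, and with few schools. If the arms differ in trauma load, migration background or share of newcomers, the only protection in the total-effect model as described is the PRE level of the same outcome.

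**Working it through.** The plan gives no figure on this point, so there is none to reproduce. The check has two parts.

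**1. What b can reflect**

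*Consent.* Recruitment was complete in August 2019. A first set of schools had been allocated before the three later schools were randomised, and one school left after allocation. Consent is tied to the start of the survey, which first ran in August to September 2019. These statements point to allocation before pupil consent, without blinding. No sentence states that order, and none says that the arm was withheld until consent.

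*Design.* The plan describes TRT as aimed at recently arrived youth with a refugee background and PIER as aimed at mixed classes. Schools were sorted by introductory class before allocation, and the three later schools could enter only INSETT+TRT or control. A baseline difference between arms can therefore arise with no fault in the random number generator.

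**2. How strong the check is**

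Inputs from Study setting and participants: 8, 3 and 5 schools, planned cluster size m = 25, ICC 0.05. Assumptions: equal cluster sizes, outcome SD of 1, two-sided 5% test, school-level t reference with k1 + k0 − 2 degrees of freedom, no covariates.

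Design effect: DE = 1 + (m − 1) × ICC = 1 + 24 × 0.05 = 2.2.

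Standard error of a baseline difference: SE = √[(DE/m) × (1/k1 + 1/k0)], with DE/m = 2.2/25 = 0.088.

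- INSETT+TRT v control (8 v 5): √(0.088 × 0.325) = 0.169 SD
- PIER v control (3 v 5): √(0.088 × 0.533) = 0.217 SD

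95% range from chance alone (critical t × SE):

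- 8 v 5, 11 df: 2.201 × 0.169 = ±0.37 SD
- 3 v 5, 6 df: 2.447 × 0.217 = ±0.53 SD

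Power to detect a true baseline shift of 0.2 SD (noncentral t, noncentrality 0.2/SE):

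| Pupils per school | ICC | 8 v 5 | 3 v 5 |
|---|---|---|---|
| 25 | 0.02 | 26% | 16% |
| 25 | 0.05 | 19% | 12% |
| 25 | 0.10 | 14% | 10% |
| 50 | 0.02 | 36% | 21% |
| 50 | 0.05 | 23% | 14% |
| 50 | 0.10 | 15% | 10% |

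The number of pupils per school is in Fig. 1, which is not shown, and could be larger. More pupils help little. As m grows, DE/m tends to the ICC, so at ICC 0.05 the SE cannot fall below √(0.05 × 0.325) = 0.127 SD or √(0.05 × 0.533) = 0.163 SD. Power then tops out at about 30% and 18%. The number of schools sets the limit.

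**The case against.** **The order of consent and allocation is not stated.** This stands. The statement that blinding was not possible concerns the trial as a whole, and a school leaving after allocation shows at most that the school knew its arm. Dates of allocation, disclosure and consent may be in a fuller protocol. A reader might infer that every pupil and parent knew the arm when consenting, and that mailed consents came in after delivery had begun. The document does not support that. The sentence on mailed consent comes just before one on T2 and T3 invitations and may refer to later waves or parent forms. For the same reason, restricting the primary analysis set by consent date is not warranted. It would not cure the problem anyway, because pupils consenting at baseline could already know their arm.

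**Any bias from selective consent is hypothetical.** This also stands. Under a normal selection model the shift is r × [λ(p2) − λ(p1)], with λ(p) = φ(z_p)/p, so that λ(0.5) = 0.798, λ(0.7) = 0.497 and λ(0.8) = 0.350. Consent of 70% v 50% with r = 0.1 to 0.3 gives 0.03 to 0.09 SD; 80% v 50% gives 0.04 to 0.13 SD. The consent rates and correlations are all assumed, and each result is below one standard error of the actual comparisons. They illustrate the mechanism and are not an estimate for this trial.

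**Little in the analysis depends on b.** Arm is estimated conditional on the PRE state, and no step is made contingent on b. That limits the harm to the estimate but does not rescue the stated interpretation. Further covariates are often left to an analysis plan. Here, however, the article itself describes the total-effect model and assigns the sociodemographics and CRIES-8 to other roles.

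**Conclusion.** The point holds as a fault of inference with a modest consequence for the model. Reading b = 0 as successful randomisation is wrong whatever the order of consent and allocation. The grouping by introductory class and the small number of schools are stated, and equality on one measured score says nothing about unmeasured factors. At the planned cluster size and ICC, a baseline imbalance of 0.2 SD would be missed about four times in five for INSETT+TRT v control and nearly nine times in ten for PIER v control. Over ICC 0.02 to 0.10 and 25 to 50 pupils per school, power is 14% to 36% and 10% to 21%.

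The figures rest on equal cluster sizes, a two-sided 5% test and no covariate adjustment. Consent after allocation is a fair inference and adds to the case, but the conclusion does not need it. The document does not show that selective entry occurred, and no size can be put on it.

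**What to change.** 1. **Total-effect models.** Add baseline variables already collected as predictors of the POST state, beside the PRE level: age, gender, native/immigrant/refugee group and T1 CRIES-8, plus the introductory-class grouping used in the allocation. The T1 value of CRIES-8 precedes the interventions, so using it does not adjust away the mediator's change. Enter time in Finland only nested within the migrant groups, because natives do not report it (Background variables).
2. **The sentence on b.** Replace it with a statement that b reflects school allocation, the grouping by introductory class and any differential consent, and is not a test of randomisation. Report the numbers of invited and consenting pupils per arm beside it.

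**Cost.** This needs wording, covariates already in the data set, and counts of invited and consenting pupils. The model spends a few degrees of freedom, including one at school level for the grouping factor, which matters with 16 schools. Precision may fall further if arm and grouping overlap strongly; the text does not say how the five control schools divide between the two groups. Covariates reduce measured imbalance only, and selection on unmeasured factors such as motivation would remain and should be named as a limitation.

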	Self-efficacy	Teachers’ self-efficacy	Teachers’ Sense of Efficacy Scale (TSES)
	Stress and work engagement	Stress symptoms	Single Item Stress Index (SISI)
		Work exhaustion/burnout	Bergen Burnout Inventory (BBI)
		Work engagement (vigor, dedication, absorption)	Utrecht Work Engagement Scale (UWES)
	Sociodemographic factors	Sex, age, teaching background, and number of students	

### Primary measures

*Psychological distress*, i.e., *internalizing and externalizing problems*, is measured with the self-report version of the Strengths and Difficulties Questionnaire (SDQ) [50] for 11–17-year-olds. SDQ is a screening questionnaire that measures 25 attributes divided into either two sub-scales of internalizing and externalizing problems or five subscales: emotional symptoms, conduct problems, hyperactivity-inattention, peer problems, and prosocial behavior. All questions are asked on a scale of “not true,” “somewhat true,” or “certainly true.” “Somewhat true” is always scored as 1, but the scoring of “not true” and “certainly true” varies with the item. For each of the five scales, the score can range from 0 to 10 if all items are completed. Goodman [51] reports SDQ to have acceptable validity and reliability (lowest in peer problems *α* .41 and highest in total difficulties *α* .80). In addition, research shows good validity for internalizing scales indicated by correspondence between children, parents, and teacher reports and clinical review [52].

*Resilience* is measured with an adapted, focus group-based Child and Youth Resilience Measure (CYRM-12) [53]. CYRM was originally designed as a 28-item measure for youth aged 9 to 23 years old. A shortened resilience measure (CYRM-12) consists of 12 items, which are scaled as 5 points (1 “not at all” to 5 “a lot”). A total score is created by summing up the score of each item. CYRM is a questionnaire exploring the individual, relational, communal, and cultural resources that may bolster the adolescents’ resilience. The participant reports on a 5-point scale as to what extent he/she feels he/she has certain resources. Preliminary results show tentative content validity of the CYRM-12 to merit its use as a screener for resilience processes in the lives of adolescents, and reliability was *α* .84.

*Posttraumatic stress symptoms (PTSD)* are screened with the Children’s Impact of Events Scale (CRIES-8) [54–56]. CRIES-8 has two sub-scales, namely intrusion and avoidance, and it is designed to be used in children aged 8 and above. The eight items are scored on a 4-point scale (0 “not at all,” 1 “rarely,” 3 “sometimes,” 5 “often”). The total score is the sum of scores from the two sub-scales. The screening cutoff is on ≤ 17 points. CRIES-8 has been applied, and its factors proved as robust in a variety of cultures. It has good construct validity and quite a stable factor structure, it correlates well with other indices of distress, and it has been used to screen very large samples of at-risk children following a wide range of traumatic events [57]. Another study [58] reported CRIES-8 to have good internal consistency (*α* .86).

